### Minimization of systematic error

To reduce potential respondent bias and maximize data integrity, a modified enrollment process will be utilized with a two-phased consent process. The first phase has a consent document focused on safety outcomes data collection rather than a comparison of the two different methodologies for collecting such outcomes. This focus is utilized to both blind participants to the comparison under evaluation and minimize dropouts as one arm (active surveillance) is more time intensive than the other (passive surveillance), but both arms are enhancements to current standard of North America practices. The second phase occurs after randomization with the consent document explaining the exact study procedures of the participant’s allocated group without reference to the other group. There will be a debrief interview at the end of a DC’s study participation to explain this modified enrollment process and the procedure for both study groups.

Other study personnel who will be blinded in the study include: (1) patients, (2) an independent biostatistician for analysis, and (3) content experts involved in the adjudication process. Because of the major differences in data management, the investigator ([name]) responsible for study coordination cannot be blinded.

### Clinical data management

All data will be entered and managed using REDCap electronic data capture tools, which is hosted at the University of Alberta [18]. REDCap is a secure, web-based application designed to support data capture for research studies.

For the active surveillance group, the data will be verified and validated, and the quality checked by a single study investigator ([name]) who will compare the patient’s pre- and post-treatment forms to ensure that inconsistencies are corrected. For audit purposes and to ensure transparency, all changes made will be recorded with the time and date and user ID. The study investigator will discuss any queries with the study team with query resolutions recorded.

### Statistical methods

The count of reported adverse events (any severity) in each group will be expressed with percentages and incidence estimates, and their 95% confidence intervals (CIs). The primary analysis will compare the cumulative incidence of adverse event reports in active versus passive surveillance. Because the outcome is number of events, it is assumed that the data will follow a Poisson distribution. Hence, a Poisson regression with log links will be used in general estimating equation (GEE) analyses with an appropriate sandwich estimator to take into account the DC cluster correlation. Groups will be compared using an intention-to-treat analysis.

Sensitivity analysis, using the same GEE analyses as above, will be conducted for reports that were not adjudicated (because of uninterpretable adverse events) and differences in how missing data were handled (i.e., imputing using average incidence and highest incidence). The binary variable expressing if the quality of the adverse event report allowed for meaningful interpretation/adjudication will be evaluated using the McNemar’s exact test because of the expected rarity of reports and cluster correlation.

Secondary analysis will address differences in the count of adverse event reports by patient-only, provider-only, and those reported by the active surveillance versus the provider-reports in the passive surveillance. Like the primary analyses, Poisson regression with log links will be used in GEE analyses to account for cluster-specific methods. Patient safety attitudes will be measured before and after participation and compared across surveillance groups.

Other planned secondary analyses are designed to identify factors associated with adverse events from the data gathered in the active surveillance group. Potential factors for adverse events include patient characteristics (e.g., age, presenting condition, sex, health history), provider characteristics (e.g., years in practice, specialty training), and treatment provided (e.g., high-velocity, low-amplitude or other). With the adverse event reports categorized by their severity (i.e., none, mild, moderate, severe, serious), logistic regression analyses will be used to model factors associated with the adverse events. If the number of moderate, severe, and serious events are small, the outcome will be dichotomized as any adverse event versus no adverse event. If numbers of moderate, severe and serious events are sufficiently large, multivariable polytomous logistic regression will be used.

Planned exploratory analyses include: (1) subgroup analysis for providers with a specialty pediatric certification and number of reported adverse events (i.e., the primary outcome); (2) assessment of the feasibility to implement a surveillance system within chiropractic offices from individual provider feedback; and (3) review of debrief interview to gain insight into participating DCs’ overall thoughts on the study, including barriers to implementation, perceived benefit of participating, and being blinded to intervention. An assessment of bias will be conducted with responding and non-responding patient demographic characteristics for the active surveillance group. All analyses will be conducted using Stata version 13 (StataCorp LP, College Station, TX, USA).

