### Recruitment, randomization, and enrollment

Licensed DCs in the United States and Canada will be recruited from a variety of venues, including pediatric chiropractic-specific events and organizations, social media, and professional newsletters/magazines. Word of mouth and referrals from colleagues and past participants will also be source of referral into the study.

As shown in Fig. 1, DCs interested in the study will complete a demographic questionnaire and review/sign the initial consent document, which states that they are interested in enrolling in a study to report safety information from 60 consecutive pediatric visits. They will then be randomized to passive or active surveillance by the study coordinator ([name]). To promote baseline equivalence, we will stratify by DC’s self-reported average proportion of pediatric patients seen (>20% versus ≤ 20%). To maintain allocation concealment, the REDCap (Research Electronic Data Capture) Randomization Module will be utilized with a random, variable, permuted block size, generated by an independent biostatistician [18]. Interested DCs will have study materials sent directly to their offices. This material includes the Consent Form that gives details on the surveillance system to which they were randomly assigned. DCs are considered enrolled in the study after that Consent Form is signed and they complete the online baseline survey, which collects additional demographic data and assesses patient safety attitudes [19]. Throughout study participation, to ensure compliance with study methods, regular communications will occur via email or telephone between the study coordinator ([name]) and the DC.

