### Sample size

An estimated active surveillance reporting rate of 4.3% and intracluster correlation of *ρ* = 0.13 were based on a pilot study of a similar active surveillance used within the chiropractic profession in Canada [20, 21]. We assumed a passive surveillance reporting rate of 0.53%, based on prior academic literature [8]. A one-sided significance level was utilized as it seems reasonable to believe that passive surveillance will result in under-reporting of adverse events [23]. We calculated that a sample size of 35 providers in each group, with each DC collecting data from 60 pediatric patient visits, and 5% one-sided significance level, would lead to 80% power. This includes an anticipated loss to follow-up of 11% of DCs and 20% of patient visits.

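### The primary Poisson GEE rests on about 8 expected passive reports; read as the usual Wald test it can have no estimate and exceeds its one-sided 5% level, and a better-behaved test costs only wording

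*Protocol article*

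**What the plan says.** The Statistical methods section of the protocol article makes the primary analysis a comparison of the cumulative incidence of reports between arms. It assumes a Poisson distribution and states that "a Poisson regression with log links will be used in general estimating equation (GEE) analyses with an appropriate sandwich estimator" to handle correlation within DCs. No covariate is named, and no rule is given for an arm without reports. The same section chooses an exact test for report quality, partly because reports are expected to be rare.

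Under Recruitment, randomization, and enrollment: "we will stratify by DC’s self-reported average proportion of pediatric patients seen", with a cut at 20%.

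Under Sample size: "An estimated active surveillance reporting rate of 4.3" per cent and an ICC of 0.13 "were based on a pilot study of a similar active surveillance used within the chiropractic profession in Canada"; "We assumed a passive surveillance reporting rate of 0.53" per cent; "a sample size of 35 providers in each group", "with each DC collecting data from 60 pediatric patient visits"; "5% one-sided significance level, would lead to 80% power". The figure allows for loss of 11% of DCs and 20% of visits.

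**The concern.** A sandwich variance relies on many clusters contributing information. Here the passive side of the rate ratio would rest on a handful of reports from very few DCs. Two problems follow if significance is judged by the usual Wald statistic.

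- With no passive report, the log rate ratio is infinite and there is no Wald test. That is the outcome most favourable to the trial's hypothesis.
- With reports from only two or three passive DCs, the sandwich variance tends to be too small, so the test rejects too often. The nominal level is already one-sided 5%, which leaves little room for inflation.

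A fallback chosen after an empty arm has been seen would be post hoc.

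**Working it through.** **Inputs.** From Sample size: rates 0.043 and 0.0053, ICC 0.13, 35 DCs per arm, 60 visits per DC, one-sided 5%, 80% power, losses of 11% and 20%. Assumed here: the between-DC distribution, which the protocol does not give, and the use of the active-surveillance pilot's ICC in the passive arm.

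**1. The plan's own figure.** Pooled two-proportion formula with mean rate 0.02415:

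n = [1.645·√(2·0.02415·0.97585) + 0.842·√(0.043·0.957 + 0.0053·0.9947)]² / 0.0377² ≈ 204 visits per arm.

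Design effect with 60 × 0.80 = 48 visits: 1 + 47 × 0.13 = 7.11. Then 204 × 7.11 / 48 = 30.2, so 31 DCs; 31 / 0.89 = 34.8, so 35. The stated 35 reproduces.

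**2. Expected passive data.** 31 × 48 × 0.0053 = 7.9 reports. Under a beta-binomial, (1 − 0.13)/0.13 = 6.69, so a = 0.0053 × 6.69 and b = 0.9947 × 6.69. The chance that one DC files nothing is B(a, b + 48)/B(a, b) = 0.926. Reporting DCs: 31 × (1 − 0.926) = 2.3.

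**3. Chance of an empty passive arm.** 0.926³¹ = 0.092. Sensitivity:

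| Setting | Risk |
|---|---|
| Beta-binomial, 31 × 48, ICC 0.13 | 9.2% |
| Gamma-Poisson, same mean and ICC | 8.1% |
| Logit-normal | 3.2% |
| Lognormal-Poisson | 1.1% |
| All-or-none mixture | 0.1% |
| Beta-binomial, no loss (35 × 60) | 5.3% |
| Beta-binomial, passive ICC 0.05 | 1.8% |
| Beta-binomial, passive ICC 0.02 | 0.4% |

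**4. Power at 4.3% against 0.53%, one-sided 5%.** An empty arm counts as no rejection for the Wald test.

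| Setting | Wald | Wald, if estimable | Permutation |
|---|---|---|---|
| Beta-binomial, 31 × 48 | 77–78% | 85% | 88–90% |
| Beta-binomial, 35 × 60 | 84% | 89% | 93% |
| Logit-normal, 31 × 48 | 87% | 90% | 92% |

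The permutation test rejected in every simulated trial with an empty passive arm. The robust score test from the same arm-only GEE had 90% power in the first setting and remains defined when the passive arm is empty.

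**5. Type I error, beta-binomial, 31 × 48, both arms at a common rate.**

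| Common rate | Wald | Permutation |
|---|---|---|
| 4.3% | 6.4–6.7% | 4.8% |
| 2.4% | 7.2–7.7% | 4.0–4.6% |
| 0.53% | 7.6–8.1% | 1.9% |

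Ranges span separate simulation runs. The score test ran at about 3–5%. A simple G/(G − 1) factor on the sandwich barely helped (6.6%, 7.6% and 7.9% at the three rates). Under logit-normal mixing at 2.4% the Wald test ran at 7.9% and the permutation test at 4.1%.

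**6. Role of the stratum.** With assumed between-stratum rate ratios of 1, 2, 4 and 8 (the protocol gives none), the Wald test without the stratum had power 77–78%. With the stratum as a covariate it had 78%, 77%, 76% and 71%. Stratified and unstratified permutation tests both gave 88–89%.

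**The case against.** The strongest reply is that the protocol never says Wald. It names a model and an appropriate sandwich, which leaves room for a small-sample correction or a score test, and the SAP is not at hand. This stands in part: the robust score test of the planned GEE performs as well as permutation, so permutation is not the only remedy. But the usual reading of the stated method is the Wald test, and that reading is worse than alternatives that cost nothing.

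Four stronger readings are tempting and are not supported.

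- **That 9% is the plan's own risk of an empty arm.** It also needs a beta-binomial, full attrition, and an ICC estimated under active surveillance applied to the passive arm. It is the top of a wide range.
- **That the plan omits the stratum, at a cost in power.** The article is silent and does not exclude it, and the covariate list may sit in the SAP. In simulation, leaving it out cost nothing and adding it gained nothing.
- **That an empty passive arm would leave nothing to report.** Each arm's incidence with a 95% interval is planned separately and would remain. What is lost is the primary comparison.
- **That a permutation test solves everything.** It gives a valid p-value with an empty arm, but no rate ratio.

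It is also fair that much of the power gap comes from scoring empty-arm trials as failures: among estimable trials Wald power is 85%. With a passive ICC of 0.05, both tests exceed 90%.

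**Conclusion.** The concern holds for the test, not for the model or the covariates. About 8 passive reports are expected whatever the mixing distribution; that they come from about two DCs depends on the ICC of 0.13 applying to the passive arm. Under a beta-binomial with that ICC, the Wald reading runs at about 7–8% instead of 5%, with about 77% power (85% when estimable), and has no estimate in about 9% of trials. Over other distributions that last risk falls to as little as 0.1%. The direction of the power and size comparison is the same under logit-normal mixing. The gain comes from the choice of test, not from adjusting for the stratum. This should be changed before the data are unblinded; it does not put the design in doubt.

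**What to change.** 1. Take the primary p-value from a permutation test of DC-level report rates that re-allocates DCs within the two randomisation strata, or from the robust score test of the same GEE. Name one in advance. Permuting within strata respects the design; it is not the source of the power.
2. Keep the GEE rate ratio as the estimate, with a named small-sample-corrected sandwich. The simple G/(G − 1) factor is not enough on the figures above.
3. State the rule for a passive arm without reports: give the rate difference with a cluster-level interval, and fix the interval method beforehand, because the observed passive variance would be zero.

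The cost is analysis wording and a short program. The stratum is already recorded and no new data are needed. One small downside is that the p-value and the model interval come from different procedures and may occasionally disagree, so the text should say which decides.

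### The missing-data sensitivity analyses treat imputed visits as observed, so an average-incidence fill understates the standard error by 0 to 29% depending on an unstated definition, and the highest-incidence interval cannot be read as inference

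*Protocol article*

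**What the plan says.** Under Statistical methods, the primary analysis is a Poisson log-link model fitted by "general estimating equation (GEE) analyses with an appropriate sandwich estimator to take into account the DC cluster correlation". The next paragraph turns to robustness: "Sensitivity analysis, using the same GEE analyses as above", is planned for unadjudicated reports and for "differences in how missing data were handled (i.e., imputing using average incidence and highest incidence". So the article names both the fill values and the model to be run on the filled data.

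It does not say whether the average is taken per DC, per arm or over both arms, what the highest incidence is the highest of, whether values are fixed or drawn, or whether DCs lost entirely are filled as well. It mentions neither multiple imputation nor any adjustment of the variance.

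Under Sample size, the 35 DCs per group allow for "anticipated loss to follow-up of 11% of DCs and 20% of patient visits".

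**The concern.** A missing-data sensitivity analysis should show at least as much uncertainty as the analysis it tests. Here the opposite can happen. The sandwich variance is built from the spread of DC totals around the fitted mean. A visit filled at the fitted mean adds nothing to that spread but does add to the denominator. The more visits and DCs are lost, the narrower the interval becomes. The sandwich estimator protects against clustering. It does not protect against values that were never observed.

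At stake is the article's stated check on missing data, which could make the active-versus-passive difference look firmer than the data allow. The article itself expects compliance to be hard, above all in the active arm (Barriers to study completion).

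**Working it through.** **Inputs (Sample size section).** Active rate 4.3%, passive rate 0.53%, ICC 0.13, 35 DCs per group with 60 visits each, losses of 11% of DCs and 20% of visits, one-sided 5%, 80% power.

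**The plan's own figure.** Two proportions at one-sided 5% and 80% power need 204 visits per arm. With 48 retained visits per DC the design effect is 1 + 47 × 0.13 = 7.11. Then 204 × 7.11 / 48 = 30.2, so 31 DCs, and 31 / 0.89 = 34.8, so 35. The stated size reproduces. The planned losses therefore leave 31 DCs × 48 visits = 1,488 observed visits out of 35 × 60 = 2,100 per arm.

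**Standard error after an average fill.** For one arm, SE(log rate) = √(Σr²) / (N × mean), where r is a DC's total residual and N the number of visits in the analysis. On observed visits N = 1,488. The arm mean, and so the log rate ratio, is the same under each within-arm fill below.

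| Average fill | Effect on r | N | SE ratio to observed visits | SE too small by |
|---|---|---|---|---|
| Arm mean, visits and lost DCs | unchanged | 2,100 | 1,488/2,100 = 0.709 | 29% |
| Arm mean, visits only | unchanged | 31 × 60 = 1,860 | 1,488/1,860 = 0.80 | 20% |
| DC's own mean for visits, arm mean for lost DCs | × 60/48 | 2,100 | 1.25 × 0.709 = 0.886 | 11% |
| DC's own mean for visits, lost DCs left out | × 60/48 | 1,860 | 1.25 × 0.80 = 1.00 | 0% |

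If both arms have the same ratio, it carries over to the log rate ratio. Fitted Poisson GEEs gave 0.709 (first row) and 0.886 (third row) under both independence and exchangeable working correlation.

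**Consequence in simulation.** Beta-binomial data at the plan's rates and ICC, keeping trials with at least one event in each arm (about 91%):

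- Coverage of the nominal 95% interval was about 72% in the first case and about 83% in the third, against 89% for the same GEE on observed visits.
- With no true difference (2% or 4.3% in both arms), the one-sided 5% test rejected in 14 to 16% of trials in the first case, against 7 to 8% on observed visits.
- One random draw per missing visit at the arm mean still left the SE about 24% below the observed-visit SE. The fault is therefore in counting filled visits as data, not only in using a constant.

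**Other fills.** With the average pooled over both arms, the mean log rate ratio fell from 2.32 to 1.24 and the SE ratio was 0.46. With the highest incidence, taken here as the highest DC rate in the arm, it fell from 2.32 to about 1.45 and the SE ratio was about 0.24.

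**The case against.** The strongest reply is that the procedure is condensed into a few words and that the level of the average, drawing and pooling normally belong in an analysis plan that is not shown. That stands as far as size is concerned: one can infer a single 29% from the planned losses, but the text does not fix it. It belongs to one reading, the arm mean applied to visits and lost DCs alike, and under another natural reading the shortfall is zero. It does not remove the point. The article does state the fill values and the unmodified model, and no average fill that was checked widens the interval.

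A second reply is that equal visit loss in both arms is doubtful. The passive arm is described only as sending incident reports, with no form for each visit, so a missing passive visit may not be recognisable. That arm, with about 1,488 × 0.0053 = 8 expected events, dominates the variance. If visits are filled at the arm mean in the active arm only, the SE ratio is about 0.86 with lost DCs filled in both arms and about 0.97 with none filled. This also stands: the effect is then smaller. The Sample size section gives its losses as allowances and does not say they will be imputed.

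A third reply is that the highest-incidence run is a bound on the estimate and was never meant to give an interval. That is a sound way to use it, but the article sends it through the same GEE without saying so.

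**Conclusion.** The concern holds in a limited form. As written, the sensitivity analyses make no allowance for visits that were never observed. For the average-incidence fill the SE is understated by 0 to 29%, depending on a definition the article does not give. The figures assume the planned losses, equal in both arms, and coverage and rejection rates further assume a beta-binomial model with ICC 0.13. The shortfall is nil only with the DC's own mean and lost DCs left out.

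The 29% does not describe the highest-incidence run, where the estimate moves and the SE falls to about 0.24 of its observed-visit value. That interval and p-value should not be read as inference.

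A reader might also infer that the main result is compromised. The documents do not support that: imputation appears only in the sensitivity analysis, and the primary GEE is not affected. The 89% coverage on observed visits is a separate small-sample matter that imputation did not cause. This should be corrected, but it does not threaten the primary conclusion.

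**What to change.** 1. State the level at which the average and the highest incidence are taken, and whether DCs lost entirely are filled.
2. Replace the single fill by multiple imputation that respects DC clusters: draw a rate for each DC within arm, draw its missing visits from that rate, run the same GEE on each data set and pool by Rubin's rules.
3. With about 8 expected passive events, a between-DC distribution may not be estimable. In that case keep the imputed point estimate but take its variance from observed visits only.
4. Report the highest-incidence run as a shifted scenario or a bound on the estimate, without treating its interval or p-value as evidence.

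The cost is analysis-plan wording, a little programming and wider sensitivity intervals. Trial conduct does not change. Within-arm imputation without further covariates will largely return the observed-visit answer, so the shifted scenario carries most of the robustness check. The undercoverage of the observed-visit GEE remains and needs its own remedy.

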**Methods/design:**

This cluster randomized controlled trial aims to enroll 70 physicians of chiropractic (unit of randomization) to either passive or active surveillance system to report adverse events that occur after treatment for 60 consecutive pediatric (13 years of age and younger) patient visits (unit of analysis). A modified enrollment process with a two-phase consent procedure will be implemented to maintain provider blinding and minimize dropouts. The first phase of consent is for the provider to confirm their interest in a trial investigating the safety of chiropractic manual therapy. The second phase ensures that they understand the specific requirements for the group to which they were randomized.

Percentages, incidence estimates, and 95% confidence intervals will be used to describe the count of reported adverse events in each group. The primary outcome will be the number and quality of the adverse event reports in the active versus the passive surveillance group. With 80% power and 5% one-sided significance level, the sample size was calculated to be 35 providers in each group, which includes an 11% lost to follow-up of chiropractors and 20% of patient visits.

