## Methods

### Study design

The study design is a pragmatic, superiority, cluster randomized clinical trial with a modified enrollment process to maintain participant blinding. DCs in private practice who treat children will be the unit of randomization with random allocation in a 1:1 ratio to active or passive surveillance reporting systems. Cluster randomization was chosen for practical reasons with the unit of analysis being reports from the individual chiropractic patient visits. The University of Alberta’s Research Ethics Board reviewed and approved this study (Pro00027903). The trial has been registered at ClinicalTrials.gov (NCT02268331). The study protocol was prepared using the Standard Protocol Items: Recommendations for Interventional Trials (SPIRIT) guidelines [16] (see Additional file 1) and also the “Methods” section of the Consolidated Standards of Reporting Trials (CONSORT) 2010 Checklist for reporting a cluster randomized controlled trial [17] (see Additional file 2).

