### Outcomes

The primary outcome will be the number (the count) and quality (i.e., ability to meaningfully interpret/adjudicate, a binary variable) of the DC’s adverse event(s) reports per patient visit and per patient in each group. Quality of adverse event reports will be assessed by the adjudicators’ ability to meaningfully adjudicate the report (section above).

A secondary outcome is the change in patient safety attitudes for participating DCs. This will be measured in both groups using the Safety Organizing Scale [19], which is a nine-item survey with a 7-point rating scale (1 – “Not at all”; 7 – “To a very great extent”). This questionnaire is to be completed at two time points: at baseline (the online baseline survey prior to study enrollment) and after adverse event data collection is complete for each participating DC. In the active surveillance arm, additional variables to assess adverse events and associated factors for adverse events include: patient-reported adverse events, manual therapy treatment description, patient health history, and patient satisfaction [22].

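### Report quality is to be compared between arms with McNemar's exact test, a paired test, although the trial has no active-passive pairs and the test does not handle clustering by doctor of chiropractic

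*Protocol article*

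**What the plan says.** The abstract of the protocol article states: "The primary outcome will be the number and quality of the adverse event reports in the active versus the passive surveillance group". The Outcomes section defines quality as the "ability to meaningfully interpret/adjudicate, a binary variable", judged on the DC's "adverse event(s) reports per patient visit and per patient in each group". For this variable the Statistical methods section plans a test that "will be evaluated using the McNemar’s exact test because of the expected rarity of reports and cluster correlation".

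The design is described elsewhere. Under Study design, DCs are "the unit of randomization with random allocation in a 1:1 ratio to active or passive surveillance reporting systems". Under Recruitment, randomization, and enrollment, the only balancing device besides permuted blocks is that "we will stratify by DC’s self-reported average proportion of pediatric patients seen". Minimization of systematic error adds that each DC is told only the procedures of the allocated group. Under Adjudication, only moderate, severe or serious events go to the content experts.

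For the count of reports, the Statistical methods section plans a Poisson GEE with a sandwich estimator for clustering by DC.

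**The concern.** McNemar's test is computed from discordant pairs, meaning units rated adjudicable under one condition and not under the other. Here each report arises in one arm only, and the arms are expected to yield very different numbers of reports, so nothing links an active report to a passive one.

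The stated reasons do not support the choice. Rarity argues for an exact or small-sample method, not for a paired one. Cluster correlation argues against it: exact McNemar treats the discordant pairs as independent and makes no allowance for several reports from one DC.

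At stake is the second half of the hypothesis, that active surveillance gives better-quality reports. An analyst following the text must either choose another test after seeing the data or run McNemar on a table that is not paired.

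**Working it through.** **1. Inputs.** From Sample size: reporting rates 4.3% (active) and 0.53% (passive), ICC 0.13, 35 DCs per group, 60 visits per DC, 5% one-sided, 80% power, losses of 11% of DCs and 20% of visits. No effect size or power is stated for quality.

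**2. The plan's own figure reproduces.**
- Two-proportion formula, one-sided 5%, 80% power, no continuity correction: 204 independent visits per group.
- Visits left per DC: 60 × 0.80 = 48. Design effect: 1 + 47 × 0.13 = 7.11.
- DCs: 204 × 7.11 / 48 = 30.2, rounded up to 31; 31 / 0.89 = 34.8, rounded up to 35.

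This concerns the count only and does not depend on the McNemar sentence.

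**3. Are there pairs?**
- Same DC under both systems: no, each DC follows one system.
- Matched DCs: no, stratified permuted blocks do not form pairs.
- Same visit or report under both systems: no, visits are nested in DCs.
- Two adjudicators on one report, or caregiver and DC in the active arm: such pairs could be formed, but they do not compare active with passive, and the text names neither.

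**4. Expected reports after stated losses (31 DCs × 48 visits = 1,488 visits per arm).**
- Active: 1,488 × 0.043 = 64.0. Passive: 1,488 × 0.0053 = 7.9.
- Without losses (35 × 60 = 2,100 visits): 90.3 and 11.1.

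These are upper-end figures for the quality variable, because only moderate or worse events are adjudicated and the documents give no severity split.

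**5. Passive DCs with any report.** This assumes that ICC 0.13, which comes from an active-surveillance pilot, also holds in the passive arm.
- Beta-binomial with a + b = (1 − 0.13) / 0.13 = 6.69 and a = 0.0053 × 6.69 = 0.0355: the probability of no report in 48 visits is 0.926, so 31 × 0.074 = 2.3 DCs report.
- With no clustering at all: 0.9947^48 = 0.775, so 31 × 0.225 = 7.0 DCs.

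**6. What happens if the test is forced.** Take 64 and 8 reports with an identical 50% adjudicable share. The arm-by-adjudicable table has off-diagonal cells 32 (active, not adjudicable) and 4 (passive, adjudicable). Exact McNemar gives 2 × P(X ≤ 4), with X binomial (36, 0.5):
- 2 × (1 + 36 + 630 + 7,140 + 58,905) / 2^36 = 133,424 / 68,719,476,736 = 0.0000019.
- At an identical 70% share the cells are about 19 and 6, and p = 0.015.

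A simulation used Poisson counts with means 64 and 7.9, the same true share in both arms, no clustering and a nominal two-sided 5% level. McNemar was run on 20,000 trials and Fisher's exact test on 3,000 of the same tables.

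| True share, both arms | McNemar rejects | Fisher rejects |
|---|---|---|
| 50% | 99.8% | 2.4% |
| 70% | 74.6% | 2.6% |
| 90% | 2.9% | 1.9% |

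The forced test compares active non-adjudicable with passive adjudicable reports. Its result depends on report volume and the overall share, not on a difference between arms. Fisher's test serves here only as an unpaired reference, since it ignores clustering too.

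**7. A tempting replacement.** Adjudicable reports per visit, with zero for DCs who file none, keeps every randomised DC in the comparison. It equals report count times adjudicable share. In simulations at the inputs of step 4 (ICC 0.13 in both arms, the same share in both arms, one-sided 5% DC-level permutation test), it rejected in about 83% to 89% of trials. As a test of quality it would mostly detect quantity.

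**The case against.** No passage rescues the sentence, so the fair defence concerns how far the point reaches.

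- **Status of quality.** A reader might infer that the trial's primary test is invalid, or that quality is a formal co-primary endpoint. The documents do not go that far. The abstract and Outcomes name number and quality together, but Statistical methods reserves the term primary analysis for the cumulative incidence of reports, the exploratory analyses gloss the primary outcome as the number of events, and only the count is powered. This stands: the status of quality is ambiguous.
- **Computability.** A reader might say that the test cannot be run. Software will return a p-value from any 2 × 2 table. The problem is that no valid pairs lie behind it.
- **Forced use.** The protocol does not say how the table would be formed, so step 6 shows what could happen and is not a planned calculation. This also stands.
- **Report numbers.** Reading 64 and 8 as the expected number of adjudicated reports goes too far, for the reason given in step 4.
- **Unseen analysis plan.** It may add detail, but the protocol already names a specific and unsuitable test, so this is not a matter left open for later.

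**Conclusion.** The point holds. The named test needs matched pairs that the design does not produce, and it does not deal with the clustering cited as a reason for it. As written, report quality, which the abstract and Outcomes include in the primary outcome, has no valid between-arm test.

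The size of the problem is illustrated by p = 0.000002 with identical quality in both arms. That figure rests on the planned reporting rates, the stated losses, a 50% adjudicable share and a forced unpaired table. The error varies with the share and nearly vanishes at 90%, so no single error rate can be given. The estimate of about 2 reporting passive DCs rests on carrying the ICC over to that arm.

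The error does not extend to the Poisson GEE for the count or to the 35 DCs per group.

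**What to change.** Replace the McNemar sentence with an unpaired, cluster-aware comparison, active versus passive, of the proportion of adjudicated reports that could be meaningfully adjudicated. This keeps the protocol's binary variable. Two suitable forms are:
- a logistic GEE with DC as cluster and a small-sample variance correction;
- a DC-level permutation test of that proportion within the two randomisation strata.

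Add three statements:
1. If too few DCs in an arm file reports for a test, the proportions are given by arm with cluster-aware intervals and no significance claim is made. The number of reporting DCs that counts as too few should be fixed before unblinding. At the plan's rates this fallback may well be what is used.
2. The comparison is conditional on a report having been filed, which allocation itself affects.
3. Adjudicable reports per visit over all randomised DCs may be added as a supplementary measure, labelled as combining quantity and quality and not as a test of quality.

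It would also help to say whether quality is part of the primary analysis. The cost is a few sentences of analysis text and a short program, with no new data and no change to the sample size. The price is an openly imprecise quality comparison.
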